### 4.2. Randomization and Blinding

The protocol involves the assignment of 52 subjects to one of three groups. Group A will comprise participants performing low-intensity training sessions within their FatMax zone. Group B will comprise participants who will perform both FatMax zone exercises as well as muscular resistance exercises (MRE). Both groups will be compared to group C, where participants will maintain their physical activity following an isoenergetic diet, evaluated through 24 h dietary records every four weeks.

For groups A and B, subjects will be allowed to perform their FatMax training on a treadmill or stationary bicycle, whichever is of their preference. The random sequence for participant assignment will be coded with SPSS 22 Software, looking for an equal distribution of both genders, BMI (overweight (≥25 and <30 kg/m^2^) and obesity grade 1 (≥30 and <35 kg/m^2^). All the evaluations and training sessions will be conducted in the Conahcyt National Laboratory of Body Composition and Energetic Metabolism (LaNCoCoME). The general process is shown in Figure 1.

To ensure single blinding, a researcher external to this study will enter data into the software on separate datasheets so that these researchers can analyze them without having access to treatment assignment information, storing all participant files in numerical order in a secure and accessible location. All files will be retained for a period of five years.

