### 2.3. Interventions or Treatments

Participants will be randomly assigned to one of three groups: Group A: Will perform low-intensity training within the FatMax zone. Group B: Will perform FatMax training combined with resistance exercises. Group C (Placebo Group): The placebo group will undergo a ‘masking training’ that does not involve significant physiological or metabolic changes. This training will consist of stretching sessions with smooth, controlled movements that do not significantly impact metabolism or induce relevant physiological changes, while maintaining the perception of physical activity and an isoenergetic diet.

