### 2.7. Control Procedures

To control potential confounding variables, participants in the control group will follow an isoenergetic diet, and dietary intake will be monitored regularly throughout this study. Individuals with less than 75% attendance at the training sessions will be excluded from the final analysis. To address potential non-compliance or dropout in this exercise intervention, a plan will be implemented that includes weekly check-ins, flexible scheduling, and the provision of motivational incentives. Close monitoring will be conducted to detect early non-compliance, with personalized support provided as needed. In cases of dropout, exit interviews will be conducted to identify barriers and improve future retention strategies. This approach aims to maximize adherence and minimize dropout throughout this study. Other variables, such as sleep quality and psychological status, will be monitored to ensure consistency across all groups.

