## 4. Detailed Procedure

### 4.1. Sample Size Calculation

To carry out the present study, 156 young sedentary adults with overweight/obesity will be recruited through a snowball sampling. Considering the body composition changes as the primary outcome, the minimum sample size calculated for the present protocol was 44 participants to reliably detect an effect size of δ ≥ 0.5, assuming a two-sided criterion for detection that allows a maximum Type I error rate of α = 0.05 with a probability of 0.9, and considering a 20% dropout of participants, the sample size has been fixed to 52 participants per group. The statistical software used to determine the sample size was G*Power (v3.1.9.7, Universität Kiel, Düsseldorf, Germany) [15]. 

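### The text ties the isoenergetic diet to the control group, the Figure 1 note gives it to every arm, and four-weekly diet records are stated for group C only

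*Protocol article*

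**What the plan says.** Four places in the protocol article say who follows the isoenergetic diet.

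- **Section 2.3 (Interventions or Treatments)** describes groups A and B by their exercise alone. For group C it describes a sham programme ("This training will consist of stretching sessions with smooth, controlled movements"), delivered "while maintaining the perception of physical activity and an isoenergetic diet".
- **Section 2.7 (Control Procedures)** states: "To control potential confounding variables, participants in the control group will follow an isoenergetic diet". It adds that "dietary intake will be monitored regularly throughout this study", with no interval and no arm named.
- **Section 4.2 (Randomization and Blinding)** describes A and B by exercise, then the comparator as "group C, where participants will maintain their physical activity following an isoenergetic diet, evaluated through 24 h dietary records every four weeks".
- **The note to Figure 1** assigns the isoenergetic diet to every participant. Section 4.2 refers to that figure: "The general process is shown in Figure 1".

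On diet recording, Section 4.5.4 gives all participants a 24 h recall before the start and at the end of the intervention, plus a food frequency questionnaire whose timing is not stated. It counts dietary patterns among the uncontrollable covariates to be monitored, yet later speaks of dietary control.

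**The concern.** A diet prescribed in the control arm alone does not control confounding. It adds a second planned difference between that arm and the others, and randomisation cannot remove a difference that the protocol itself introduces after allocation.

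The affected comparisons are the main ones. Section 4.2 says "Both groups will be compared to group C", and Section 4.1 sizes the trial "Considering the body composition changes as the primary outcome". Diet bears directly on that outcome. Closer diet recording in one arm is a further difference in contact, and it also makes measured intake less comparable between arms.

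**Working it through.** The plan gives no figure to reproduce. The check is a comparison of the text, followed by two simple counts.

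**1. Who follows the diet**

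- Section 2.3: stated for C; nothing on diet for A or B.
- Section 2.7: stated for the control group, as the measure against confounding.
- Section 4.2: stated for C; nothing on diet for A or B.
- Figure 1 note: stated for all participants.
- Section 4.5.4: monitoring for all; no statement on who is prescribed the diet.

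Three sections attach the diet to C and one figure note attaches it to everyone. No sentence excludes A or B, and no sentence says that the note takes precedence over the text.

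**2. What each reading does to the contrasts**

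- *Diet in C only.* A-C compares FatMax without the diet rule against stretching with it. B-C compares FatMax plus resistance without the rule against stretching with it. A-B carries no diet difference. Affected: 2 of 3 contrasts.
- *Diet in all arms.* No contrast carries a difference in the diet rule. Affected: 0 of 3. The stated recording schedules would still differ.

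**3. Whether the analysis in Section 4.5.5 repairs the first reading**

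- The between-treatment ANOVA has no covariates, so it does not.
- The regression adjusts for dietary variables. Let a and b be the indicators for arms A and B, with C as reference. An indicator for the diet rule would be 1 − a − b. That is an exact linear function of the intercept and the arm terms, so the rule and the arm cannot be separated.
- Measured intake is not the same as the rule and does vary within arms. But intake before the start cannot reflect a diet imposed afterwards, and intake at the end is itself a result of the assigned arm. Adjusting for it does not cleanly recover the exercise effect.

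**4. Stated diet-intake time points**

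- Group C: 16 weeks / 4 = 4 records (weeks 4, 8, 12 and 16, Section 4.2). Adding the recall before the start (Section 4.5.4) gives 4 + 1 = 5, counting the end recall and week 16 as one occasion.
- Groups A and B: before the start and at the end (Section 4.5.4) = 2. This is a minimum, because Section 2.7 promises regular monitoring without a schedule.
- The food frequency questionnaire is left out of both counts, since it applies to all arms and its timing is not given.

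**5. Cost of an equal schedule**

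- Extra time points per participant in A and B: 5 − 2 = 3 (weeks 4, 8 and 12).
- Participants in A and B at full enrolment: 2 × 52 = 104.
- Extra records: 3 × 104 = 312 at most. If A and B are already recorded every four weeks, the number is 0.

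No bias is calculated, because the document gives no effect of the diet on body composition.

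**The case against.** The strongest reply is that the passages can be reconciled. Saying that C follows the diet does not say that A and B do not. The Figure 1 note is explicit and covers everyone, and Section 4.2 sends the reader to that figure. On this reading every sentence is true, whereas a C-only diet would make the note false. Section 4.5.4 also monitors intake in all participants, and the monitoring clause in Section 2.7 names no arm. The harm is then conditional, its size is unknown, and individual intakes are available for adjustment.

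Much of this stands. The all-arm reading is possible, no arm is expressly excluded, and under that reading the diet confounding is gone. The count of two time points for A and B is a minimum, so 312 is an upper bound. The regression could also use individual intakes.

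It does not remove the point. A condition named for one arm in three sections, and in one of them as the safeguard against confounding, will reasonably be run and reported as specific to that arm. Condensation into an article can explain missing detail, but not two printed statements of different scope. The four-weekly records are stated for C alone, and neither Section 4.5.4 nor the unscheduled monitoring in Section 2.7 extends them to A and B. Adjustment for intake has the limits shown in the working.

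**Conclusion.** The concern holds. The article contradicts itself on the scope of a co-intervention that bears on the primary outcome, and it gives two diet-recording schedules, the denser one for group C alone. Run as Sections 2.7 and 4.2 are worded, A-C and B-C (2 of 3 contrasts) do not isolate exercise. Run as the Figure 1 note is worded, none is confounded by the diet rule.

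The inconsistency is certain; which version is carried out is not. The counts of five against at least two time points assume that four-weekly means weeks 4, 8, 12 and 16 and that the end recall coincides with week 16. The size and direction of any bias are unknown. This should be corrected, but it does not show that the primary comparisons are in fact confounded.

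**What to change.** - Bring Sections 2.3, 2.7 and 4.2 into line with the Figure 1 note: the same isoenergetic diet instruction in groups A, B and C.
- In Sections 4.2 and 4.5.4, set one 24 h record schedule for every arm: baseline and weeks 4, 8, 12 and 16. Refer to that schedule in Section 2.7.
- If the diet is in fact meant to differ by arm, say so, and describe A-C and B-C as comparisons of packages: exercise without the diet rule against stretching with it.
- While editing Section 4.2, make the description of group C match Section 2.3: it attends the stretching sessions and otherwise keeps its habitual activity. This is a side point on which the conclusion does not depend.

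The cost is protocol wording plus up to three extra records per participant in A and B, at most 312 at full enrolment and none if those arms are already recorded every four weeks. Sample size and analysis methods need not change.

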### 4.3. Pre Intervention Exercise Test

Energy expenditure and the utilization of fat and carbohydrates at rest and during exercise will be determined by indirect calorimetry using a Metabolic Measurement System (TrueOne 2400, Parvomedics, Sandy, UT, USA), calibrated before each measurement. For basal metabolism, the subjects will remain in the Fowler anatomical position (semi-sitting supine) for continuous measurement of oxygen consumption (VO_2_) and carbon dioxide production (VCO_2_) for a period of 15 to 20 min. Subsequently, the average values of the VO_2_ and VCO_2_ recorded during a stable phase of 5 min (coefficient of variation in RQ ≤ 5%) and used to calculate energy expenditure and the macronutrient oxidation rate, using the stoichiometric equations of Weir [16] and Frayn [17], respectively.

A graded exercise protocol previously validated by the working group associated with the LaNCoCoME (Table 2) will be used to determine cardiorespiratory fitness, metabolic flexibility, and fat oxidation biomarkers. Briefly, this protocol allows an estimation of macronutrient oxidation at FatMax with a measurement error of ~1.6 g/h for carbohydrate oxidation and ~1.3 g/h for fat oxidation [18]. Distinct parameters of cardiorespiratory fitness and metabolic flexibility will also be determined by a maximal stress test exercise test on one treadmill (Quinton TM55, WA, USA) or cycle ergometer (Monark Exercise AB, Vansbro, Sweden), as described in Table 2.

Gas exchange and heart rate (Polar H10, Polar^®^ Electro OY, Kempele, Finland) will be recorded throughout the exercise tests, while the rate of perceived exertion will be registered at the end of each stage using the modified Borg scale with a 0–10 rating. The average VO_2_ and VCO_2_ values of the last 2 min of each stage before RER ≥ 1.0 will be used to calculate fat and carbohydrate oxidation using the stoichiometric equations of Jeukendrup and Wallis [19]. The maximum rate of fat oxidation and its corresponding intensity during exercise will be determined by mathematical modeling of fat oxidation kinetics, plotted against oxygen consumption (% VO_2_max) [20]. The symmetry, amplitude, and translation parameters of the curve will be calculated as well to represent the oxidative capacity of each subject.

Additionally, fat oxidation kinetics will be used to determine two new metabolic flexibility indices described by the following analytical procedures: (i) calculation of the area under the curve corresponding to fat oxidation kinetics; and (ii) simple linear regression to determine the increase in fat oxidation concerning the change in energy expenditure during the transition from rest to FatMax [21]. Both metabolic biomarkers will be calculated with GrapPad Prism v8.1 software and will be interpreted as follows: The higher the value, the better the metabolic flexibility.

The lactate and ventilatory thresholds will also be computed in ExPhysLab (https://www.exphyslab.com/, accessed on 26 October 2024), using a computerized algorithm that allows the automatic detection of these biomarkers through 25 distinct approaches [22]. Baseline blood lactate concentrations will be considered for the fitting of blood lactate kinetics by using a 3rd degree polynomial regression in all participants. Furthermore, the nine-panel approach proposed by Wasserman and Mcllroy [23] will be used to determine the ventilatory thresholds. The efficiency of oxygen consumption and the optimal breathing point will be determined by analyzing the relationship between dynamic pulmonary ventilation and oxygen consumption. The maximum oxygen consumption (VO_2_max) will be verified using the following criteria: (i) a VO_2_ plateau (increase in VO_2_ < 150 mL/min) during the final stage of the exercise protocol; (ii) RER ≥ 1.15; (iii) LA−max ≥ 8.0 mmol/L; and (iv) heart rate ≥ 90% of the theoretical maximum heart rate. The cut-off points provided by the American College of Sports Medicine will be used to determine the cardiorespiratory fitness level of the participants according to their age and sex [5]. Finally, blood lactate concentration will be measured using a portable lactate analyzer (Nova Biomedical Corp., Waltham, MA, USA). The lactate threshold will be determined by plotting the data and identifying the precise point corresponding to a 4 mmol/L concentration.

### 4.4. FatMax and Resistance Training: Frequency, Intensity, Time and Type

The characteristics of FatMax and resistance training are described in Table 3. In brief, the training sessions at FatMax will begin with a 5 min warm-up at 4 km/h (1°) or 50 w (60 rpm). Afterward, each patient will exercise on the treadmill or stationary bike for 40 min at their corresponding FatMax heart rate (±5 beats/min). The training volume will gradually rise up to 240 min/week, assessing gas exchange every four weeks to examine the acute metabolic response to prolonged exercise at FatMax and calculate fat utilization as recommended by Chávez-Guevara et al. [18].

In the case of resistance training, each session will have a warm-up phase of 5–10 min and a main physical conditioning phase of 30–40 min that will consist of developing a personalized circuit of strength exercises of the main muscle groups (arms, shoulders, chest, back, and legs) at moderate intensity, finishing with a cool-down of 5–10 min.

To reduce the possibility of molecular interference between FATmax training and resistance exercise, these sessions will be scheduled at least 6 to 8 h apart, ensuring adequate time for distinct physiological adaptations to each exercise modality.

### 4.5. Baseline and Follow-Up Measurements

#### 4.5.1. Biochemical Variables

Two blood samples will be collected per participant (8 mL after 8–10 h of fasting) during the clinical trial, the first on day 0 and the second at the end of the intervention (day 112). To ensure results that more accurately reflect the organism’s basal state, post-exercise biochemical measurements will be taken at least two days after the intervention, avoiding the temporary alterations caused by acute physical exertion. Plasma samples will be obtained by refrigerated centrifugation at 3000× *g* for 20 min and frozen at −80 °C until further analysis. Plasma samples will be processed for total cholesterol, high-density lipoprotein cholesterol (c-HDL), low-density lipoprotein cholesterol (c-LDL), triglycerides, glycosylated hemoglobin, and glucose by standard colorimetric procedures following the manufacturer’s instructions (Spinreact, Girona, Spain) with a Mindray BS200 biochemical autoanalyzer (MINDRAY, Shenzhen, China). Additionally, plasma IL-6 and TNF-α concentrations will be evaluated with the Quantikine immunoassay kit from R&D Systems (Minneapolis, MN, USA) and a sensitivity ELISA kit with an alkaline phosphatase signal amplification system, respectively (Quantikine HS, high sensitivity, R&D Systems, Minneapolis, MN, USA).

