### 2.4. Dependent Variables

The dependent variables include body composition (fat mass and muscle mass), biochemical parameters (glucose, cholesterol), metabolic markers (fat and carbohydrate oxidation rates), and epigenetic markers (microRNAs associated with adipogenesis and fat metabolism).

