### 3.1. Biochemical Variables

Blood samples will be collected in EDTA vacutainer tubes and centrifuged at 3000× *g* for 20 min at refrigerated temperatures. Samples will be stored at −80 °C until analysis. Total cholesterol, c-HDL, c-LDL, triglycerides, glycosylated hemoglobin, and glucose levels will be measured using standard colorimetric procedures, following the manufacturer’s instructions (Spinreact, Girona, Spain), and analyzed with a Mindray BS200 biochemical autoanalyzer (MINDRAY, Shenzhen, China). Plasma concentrations of IL-6 and TNF-α will be assessed using Quantikine immunoassay kits (R&D Systems, Minneapolis, MN, USA).

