#### 4.5.3. Epigenetic Variables

To measure circulating microRNAs, peripheral venous blood samples will be collected in EDTA vacutainer tubes (5 mL). Subsequently, the mirVana™ miRNA Isolation Kit (Thermo Fisher Scientific, Waltham, MA, USA) will be used to analyze 14 microRNAs involved in inflammatory processes (miR-15, miR-29c, miR-30^a^, miR-142/3, miR-181^a^), adipogenesis (miR-188-5p, miR-146b-5p, miR-103, miR-107, miR-125b), and fatty acid metabolism (miR-33, miR-335, miR-370, miR-758).

Additionally, cDNA synthesis will be carried out through the reverse transcription of the microRNAs using the TaqMan MicroRNA-RT Kit (Thermo Fisher Scientific, Waltham, MA, USA). Specifically, amplification of the microRNAs of interest will be performed using the TaqMan Universal Master Mix II with UNG reagent (Thermo Fisher Scientific, Waltham, MA, USA). The specific amplification of each microRNA will be conducted with the QuantStudio 3 system (Thermo Fisher Scientific, Waltham, MA, USA), using probes specific to each microRNA and their internal controls through the TaqMan MicroRNA Assays MTO LG chemistry (Thermo Fisher Scientific, Waltham, MA, USA). The relative quantification of expression levels will be performed using the ∆∆Ct quantification method, validated through the quantification of amplification efficiency and the construction of a dynamic range curve.

In turn, the genetic influence on anthropometric and biochemical changes after the treatments will be evaluated using TaqMan probes (Thermo Fisher Scientific, Waltham, MA, USA) through an RT-PCR system using a StepOnePlus thermocycler (Thermo Fisher Scientific, Waltham, MA, USA). The polymorphisms to be assessed will include those related to obesity (rs9939609, *FTO*), lipid metabolism (rs1799883, *FABP2*), and physical adaptation to exercise (R577X, *ACTN3*). Genotyping will be verified using positive controls corresponding to the three possible genotypes in each experiment.

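### Section 4.5.1 assigns glycosylated hemoglobin to frozen plasma, which cannot give a valid value, and no section names a red-cell-containing specimen for it

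*Protocol article*

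**What the plan says.** Section 4.5.1 describes the blood work in one continuous sequence.

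- **Draw:** "Two blood samples will be collected per participant (8 mL after 8–10 h of fasting"), on day 0 and at the end of the intervention (day 112).
- **Preparation:** "Plasma samples will be obtained by refrigerated centrifugation".
- **Storage:** "frozen at −80 °C until further analysis".
- **Assay:** "Plasma samples will be processed for total cholesterol, high-density lipoprotein cholesterol (c-HDL), low-density lipoprotein cholesterol (c-LDL), triglycerides, glycosylated hemoglobin, and glucose", by colorimetric methods on the autoanalyzer.

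Section 3.1 gives a parallel account: "Blood samples will be collected in EDTA vacutainer tubes and centrifuged", then storage at the same temperature, then the same analytes, including "triglycerides, glycosylated hemoglobin, and glucose levels will be measured using standard colorimetric procedures". That list names no specimen. Section 3.1 uses the word plasma only for IL-6 and TNF-α.

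Section 4.5.3 describes one further collection, for microRNA: "peripheral venous blood samples will be collected in EDTA vacutainer tubes (5 mL"). Section 2.4 gives the biochemical dependent variables as "biochemical parameters (glucose, cholesterol") and does not mention glycosylated hemoglobin.

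**The concern.** Glycosylated hemoglobin is a property of the hemoglobin inside red cells. Centrifuging anticoagulated blood and taking the plasma separates those cells from the specimen. Any hemoglobin found in plasma has leaked through incidental hemolysis, so a reading from it would be missing or artefactual.

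At stake is the only longer-term glycemic measure in the assay lists. The other glycemic analyte is fasting glucose, taken at two time points. Section 5 anticipates better insulin sensitivity and a lower risk of type 2 diabetes, yet neither Section 3.1 nor Section 4.5.1 lists an insulin assay. Without a valid glycosylated hemoglobin, fasting glucose would carry the glycemic evidence alone.

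**Working it through.** The plan states no figure to reproduce, and the point does not depend on power, alpha or effect size. The check is whether any section gives this analyte a specimen that contains red cells.

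**Step 1. Specimen, section by section**

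| Section | Handling | Specimen stated for glycosylated hemoglobin |
|---|---|---|
| 3.1 | EDTA tube, centrifuged, frozen | None stated; no whole-blood or hemolysate step |
| 4.5.1 | Plasma obtained by centrifugation, frozen | Plasma, stated positively |
| 4.5.3 (microRNA) | 5 mL EDTA tube; processed to plasma or serum within 2 to 4 h | Not assigned to this analyte |
| 4.5.3 (genotyping) | Source of the DNA not stated | Not assigned to this analyte |

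One section names a specimen, and it is the wrong one. One names none. No section assigns whole blood, packed cells or a hemolysate to glycosylated hemoglobin.

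**Step 2. Standing of the variable**

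- Primary outcome (Section 4.1): change in body composition. Not affected.
- Dependent variables (Section 2.4): glucose and cholesterol for biochemistry. Glycosylated hemoglobin is not named.
- Abstract: cholesterol, glucose, triglycerides and inflammatory markers. Glycosylated hemoglobin is not named.
- It appears only in the assay lists of Sections 3.1 and 4.5.1.

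**Step 3. Extent**

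- Autoanalyzer analytes: total cholesterol, c-HDL, c-LDL, triglycerides, glycosylated hemoglobin and glucose, so 1 of 6 is affected.
- Ceiling: 52 per group × 3 groups = 156 participants, and 156 × 2 draws = 312 determinations.
- With the 20% dropout allowed for in Section 4.1, and assuming that every participant gives the day 0 sample and that dropouts miss only the day 112 sample: 156 + 0.80 × 156 = 156 + 124.8, or about 281 determinations.

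These are counts of measurements. They do not measure an effect on any trial conclusion.

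**The case against.** The best case on the other side is that this is a slip of grouping in a condensed article. The assays are to follow the manufacturer's instructions, and the laboratory may in practice handle this analyte correctly. A slip is indeed the likeliest cause. But Section 4.5.1 does more than leave the specimen to another document: it names plasma. An instruction about how to run the assay does not change which material has been stored. If the full laboratory procedure uses whole blood, the published sentence contradicts it; if it uses plasma, the measurement fails. The sentence needs correcting either way.

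Three stronger readings are tempting, and the document does not support them.

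- **That both sections send this analyte to plasma.** Only Section 4.5.1 does. Section 3.1 lists it after centrifugation and storage without naming a specimen.
- **That the loss is certain and cannot be repaired after the baseline draw.** No section says that the cells are discarded. Genotyping in Section 4.5.3 needs material that contains DNA, and its source is not given, so the article evidently does not list every fraction kept. A usable red-cell-containing fraction may exist.
- **That a named trial outcome is lost.** The analyte is in the assay lists but not among the dependent variables or the parameters in the abstract. No stated hypothesis, sample-size input or named analysis rests on it.

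The objection therefore stands on weight and on irreversibility. It does not stand on the wording of Section 4.5.1.

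**Conclusion.** The point holds as an error in the stated specimen. Followed as written, the plasma described in Section 4.5.1 would give no valid glycosylated hemoglobin at either time point, and no other section supplies a suitable specimen.

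The weight is modest. This is a biochemical measurement outside the primary outcome, with a ceiling of 312 determinations before dropout. The lipids, glucose, cytokines, microRNAs, calorimetry and body composition are untouched. The practical consequence is that fasting glucose would be the only glycemic measure.

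The conclusion rests on two things. One is elementary specimen knowledge: hemoglobin is in the red cells. The other is a condition the article leaves open: that no red-cell-containing fraction is kept for this analyte. If one is kept, the defect reduces to a wrong sentence.

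**What to change.** Amend Sections 3.1 and 4.5.1 together:

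1. State that an aliquot of EDTA whole blood from the tube already drawn is set aside before centrifugation for glycosylated hemoglobin, at day 0 and at the end of the intervention.
2. Restrict plasma to the lipids, glucose and cytokines.
3. If no such aliquot is to be kept, delete glycosylated hemoglobin from the measurements.

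The cost is one aliquot per draw and a sentence in the laboratory procedure, with no extra visit or venepuncture. If baseline sampling has already begun, first establish what fractions were retained, because that decides whether day 0 values can still be obtained.
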